**Tab. 2: Working Hypotheses of the Overall Project**

|              |                                                                                                                  |
|--------------|------------------------------------------------------------------------------------------------------------------|
| Hypothesis 1 | There are modifiable risk factors for the restoration of work ability in the cross-sector treatment process.     |
| Hypothesis 2 | These factors also play a relevant role in the post-traumatic condition of the patient regarding hrQoL.          |
| Hypothesis 3 | PREMs assist in identifying such factors and in developing recommendations and measures to improve patient care. |

*hrQoL = health-related quality of life; PREMs = patient-reported experience measures*

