## **Follow-Up Assessments**

Follow-up assessments will be conducted 6, 12, and 18 months after the trauma, including the PREM and PROM developed in the project (see Figure 2). The optimal follow-up assessment processes will be developed based on the results of patient interviews, literature research, and discussions with stakeholders from previously conducted follow-up studies on severely and critically injured patients, while considering data protection and technical conditions. For the follow-up, patients will be surveyed either by mail or by phone from the respective study clinics. They will not be summoned by the study clinics. In an initial work package of the overall project, a patient group-specific assessment methodology for follow-up will be developed. If postal surveys prove to be the best method of inquiry for this patient group, responses will be returned to the treating study clinic. Other partners will not have knowledge of the patients' identities.

Figure 2: Flowchart of the Prospective Cohort Study LeAf Trauma

\*FU = Follow Up, GCS = Glasgow Coma Scale, MAIS = Maximum Abbreviated Injury Scale

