### **7.1.5 Data Collection for the Prospective Cohort Study (Baseline and Follow-Up)**

Patients will be surveyed a total of four times in the prospective arm of the study (baseline, 6, 12, and 18 months follow-up). At the time of discharge from the study clinic, a baseline survey will be conducted, followed by the follow-up collection of Patient-Reported Outcomes (PROs) regarding health-related quality of life (hrQoL) and work ability (AF), as well as an evaluation of the treatment pathway experienced by the patient (Patient-Reported Experiences (PREs)). The collection of patient data will be conducted via a questionnaire. The questionnaire will consist of several modules. Validated questionnaires will be used whenever possible. The measurement instruments listed under "Assessment of Influences on Work Ability after Trauma (PROM)" and "Patient-Reported Experience Measures (PREMs)" will be selected based on the patient and expert interviews and supplemented with independently constructed questions. The completion of the questionnaire should not take longer than 30

minutes. Before the start of patient recruitment, the questionnaire will undergo a pretest and will be revised as necessary.

- **TraumaRegister DGU Standard Form** (only during baseline survey, see attached documents)
- **Assessment of Quality of Life after Trauma (PROMs)**
  - POLO Chart  
- **Assessment of Influences on Work Ability after Trauma**
  - Health-related factors (physical and psychological)
  - Sociodemographic factors
  - Individual factors and personality structure
  - Rehabilitation-related factors
  - Workplace-related factors
  - Injury characteristics and information regarding the hospital stay
- **Patient-Reported Experiences (PREMs)**
  - Treatment and care in the acute clinic
  - Assessment of medical interfaces in the patient pathway
  - Description of organizational hurdles with authorities and institutions

It is expected that additional characteristics of patient experience in the treatment pathway will be highlighted in the patient and expert interviews; these will be considered in the construction of the questionnaire.

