## 7.2 Statistical Analysis

- **Description of Progress:** All patients; description of the regaining of work ability (AF) and health-related quality of life over time (3 follow-up points; descriptive statistics).
- **Predictors for AF:** AF up to 18 months after trauma as a yes/no criterion; univariate and multivariate analysis (logistic regression) of possible predictors; classification of predictors into the categories: patient, profession, pre-hospital, clinic, post-acute therapy, presence of psychological problems (from QoL assessment at follow-up time).
- **Predictors for Time until AF:** Only patients with regaining AF: Time until AF as a dependent variable, Kaplan-Meier curves for description, Cox regression for multivariate analysis, predictors as above.
- **Health-related Quality of Life and PREMs:** Description at the 3 follow-up points, correlation with AF as subgroup comparisons at each measurement time.

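### Psychological problems measured at follow-up are used to predict work ability regained at any time up to 18 months, with no requirement that the measurement come first; post-acute therapy has the same gap, to a degree that depends on its coding

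*Protocol*

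**What the plan says.** Protocol section 7.2 defines the outcome of the main predictor analysis as "AF up to 18 months after trauma as a yes/no criterion" and plans "univariate and multivariate analysis (logistic regression) of possible predictors". The predictor categories are patient, profession, pre-hospital, clinic, and then "post-acute therapy, presence of psychological problems (from QoL assessment at follow-up time".

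The time-to-AF analysis takes over the same list: "Cox regression for multivariate analysis, predictors as above".

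Under Follow-Up Assessments the protocol states: "Follow-up assessments will be conducted 6, 12, and 18 months after the trauma". Section 7.1.5 has quality of life and work ability collected together at these follow-ups.

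The protocol does not say which follow-up supplies the psychological variable, does not require it to precede AF, and gives no time window for post-acute therapy. Hypothesis 1 in Tab. 2 shows what the models are for: "There are modifiable risk factors for the restoration of work ability in the cross-sector treatment process".

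**The concern.** A logistic model has one value per patient for each predictor, and here the outcome window runs from trauma to 18 months. A psychological value taken at 6, 12 or 18 months is, for many patients, recorded after AF was regained or at the visit where AF is reported. The model cannot separate poor mental state delaying AF from continued inability to work worsening mental state.

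Post-acute therapy raises a related question. If it is coded as ever received, and a patient can regain AF before a late start, those who recover early have less chance to be counted as treated. Therapy can then look like a barrier. Section 4 of the protocol says that rehabilitation is often delayed, so late starts are realistic.

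The study aims to identify modifiable determinants and derive recommendations from them. Both categories are natural candidates for that label.

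**Working it through.** **Plan's own figure.** Section 6.3.1 says about 30 predictors can be examined: 0.30 × 1000 / 10 = 30. This reproduces. The plan gives no figure for the timing problem, so the rest is illustrative.

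**Inputs from the protocol.** Follow-ups at 6, 12 and 18 months. AF proportion of 70% (section 6.3.1 assumes about 30% have not resumed work) or 30% (the pilot-study figure in section 4, given there for two years).

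**Assumptions.** Constant AF hazard λ from month d (d = 0, 2 or 3), so λ = −ln(1 − F)/(18 − d), where F is the AF proportion at 18 months. Psychological problems have no effect on AF. Their prevalence is 40% without AF, and AF halves the odds: 0.667 becomes 0.333, a prevalence of 25%.

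**Psychological status.**

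1. Share of AF events that precede the visit at month v: s = (1 − e^(−λ(v−d)))/F. For F = 0.70, d = 0, v = 6: λ = 0.0669 and s = 0.3306/0.70 = 0.47. For F = 0.30: λ = 0.0198 and s = 0.1121/0.30 = 0.37. At v = 12 the shares are 0.79 and 0.71.
2. Prevalence at the visit among patients with AF by 18 months: 0.25s + 0.40(1 − s). For F = 0.70, d = 0, v = 6: 0.329, odds 0.491.
3. Odds ratio against patients without AF: 0.491/0.667 = 0.74.

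| AF by 18 months | AF possible from month | 6-month value | 12-month value | 18-month value |
|---|---|---|---|---|
| 70% | 0 | 0.74 | 0.59 | 0.50 |
| 70% | 3 | 0.82 | 0.61 | 0.50 |
| 30% | 0 | 0.79 | 0.63 | 0.50 |
| 30% | 3 | 0.86 | 0.65 | 0.50 |

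Every entry should be 1. In simulated cohorts of 1000 using the value at the end of follow-up, the odds ratio was 0.48 to 0.51, with p < 0.05 in every replicate.

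**Landmark check.** Among patients without AF at the visit, the prevalence is 40% whether or not AF follows, so the odds ratio is 1. A simulation with d = 0 gave 0.98 to 1.00 at the 6- and 12-month landmarks.

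**Post-acute therapy, if coded as ever received before AF.** Further assumptions: 60% are due to receive therapy, its start is exponential with mean m months, it has no effect, and it is recorded only if begun before AF. The share of AF patients due for therapy who regain AF first is u = e^(−d/m) × λ/(λ + 1/m) × (1 − e^(−(λ+1/m)(18−d)))/F. Exposure is 0.6(1 − u) with AF and 0.6(1 − e^(−18/m)) without.

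For F = 0.70, d = 0, m = 4: u = 0.3005, exposure 0.4197 against 0.5933, odds 0.723 against 1.459, odds ratio 0.50. The other cases at F = 0.70:

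| AF possible from month | m = 1 | m = 2 | m = 4 |
|---|---|---|---|
| 0 | 0.80 | 0.66 | 0.50 |
| 2 | 0.97 | 0.84 | 0.63 |
| 3 | 0.99 | 0.90 | 0.69 |

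Simulation gave 0.51 to 0.78 for d = 0 and 0.62 to 0.99 for d = 2 or 3. As m approaches 0 (start at discharge), u approaches 0 and the odds ratio approaches 1. A Cox model in all patients with time-dependent therapy recovered the null: hazard ratios 0.99, 1.01 and 0.99 for median starts of 3, 6 and 12 months.

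**The case against.** Much can be said against a broader form of this point.

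- A reader might infer that the Cox model uses time-fixed covariates. Section 7.2 does not say so. Time-dependent coding fits its wording and is commonly left to the SAP, which is not at hand.
- A reader might infer that post-acute therapy can accrue only while the patient is unable to work. The protocol does not say this; its treatment pathway includes outpatient follow-up, which may continue after AF.
- The therapy variable is not defined. Section 4 speaks of rehabilitation quality and timing, and section 7.1.5 of rehabilitation-related factors. An ever-received indicator is only one possible coding.
- The therapy figures depend heavily on whether AF is possible from day 0. With no AF in the first 2 to 3 months, a mean start of 1 month gives almost no bias.
- A reader might infer that the recommendations would rest on artefacts. The protocol compiles findings from interviews, routine data and expert evaluation as well, and section 7.2 separately plans a descriptive comparison of quality of life with AF at each visit.

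These objections stand, and they limit the therapy and Cox parts to a conditional statement. They do not remove the main point. Section 7.2 itself fixes the psychological predictor as a follow-up measurement and the outcome as AF at any time up to 18 months. Time-dependent coding in the Cox model cannot repair the logistic model, and the separate descriptive comparison does not take the variable out of it.

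**Conclusion.** The point holds for psychological status in the logistic model as written: the predictor can be measured after the outcome or together with it. If AF halves the later odds of psychological problems and there is no effect in the other direction, the odds ratio with 70% AF is about 0.74 to 0.82 using the 6-month value and 0.5 using the 18-month value. With 30% AF the 6-month figure is 0.79 to 0.86. The halving, the 40% prevalence and the constant hazard are assumptions; the ordering problem does not depend on them.

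For the Cox model the problem is that the same predictors are carried over with no stated ordering. For post-acute therapy it is that no exposure window before AF is given. Bias there is possible, ranging from strong (late start, ever-received coding) to negligible (start at discharge). The documents do not support saying that it will occur.

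**What to change.** In section 7.2, require that every predictor be measured before AF, and then:

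- keep predictors known at discharge in the full-cohort logistic model;
- analyse psychological status and post-discharge therapy by landmark (values at 6 months, in patients without AF by then, predicting AF between 6 and 18 months; likewise at 12 months), or as time-dependent covariates in the Cox model;
- report psychological values from the same visit as AF, or a later one, as association only, not as modifiable risk factors.

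No new visits are needed. The cost is wording, programming and precision. With 1000 patients and AF possible from day 0, 70% AF leaves 1000 × (1 − 0.3306) = 669 patients at the 6-month landmark, of whom 700 − 331 = 369 regain AF later and 300 do not. With 30% AF, 888 remain and 300 − 112 = 188 regain AF later. The 12-month sets are smaller: 448 patients with 148 later AF events, or 788 with 88. At 10 events per factor, 88 events support about 8 predictors, so the 12-month models would need a short list.

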## **4. Scientific Background**

In Germany, approximately 30,000 people suffer a severe trauma each year (annual reports of the “Trauma Register DGU”). In recent decades, significant progress in preclinical and clinical treatment has markedly reduced the mortality rate of severely injured patients (Ruchholtz et al., 2008). With increasing survival rates, the functional outcomes and health-related quality of life of these patients are becoming more important. Affected patients suffer from chronic pain, psychosomatic disorders, and unemployment (Simmel et al., 2010; Simmel et al., 2013), as well as increased post-traumatic morbidity (Bouillon et al., 1998; Holtslag et al., 2007; von Rüden et al., 2013).

The return of patients to the workforce is important to promote their quality of life and social participation and to reduce the socioeconomic burden on society due to disability. According to current data from the “Trauma Register DGU,” 60% of severely injured patients in Germany are of working age (18-65 years), and three-quarters are male. With a current legal retirement age of 67 years, disability can lead to a financial gap of several decades. The high unemployment rate after trauma is well-known. According to the Hannover Polytrauma Long-Term Study (HLPS) (Sittaro et al., 2007), an average of about 22% of patients who were previously able to work are unemployed. Another 16% have undergone retraining due to their

accident to maintain work ability, and 24% have been classified for early retirement due to the accident. According to a Dutch study, only 58.5% of the severely injured patients of working age who were followed up were able to engage in full-time employment 15 months after the trauma, and an additional 21.5% could only pursue part-time employment (Holtslag et al., 2007). According to data from a pilot study on outcome assessment, only about 30% of all severely injured patients in Germany are able to work again two years after an accident (Kamp et al., 2019).

Following predictors of clinical treatment for disability have already been identified: patient age, severity of injury, traumatic brain injury, duration of intensive medical treatment, psychological sequelae, subjective perception of the injury, and the patient's education level (Frink et al., 2014; Kaske et al., 2014).

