### **5.1 Research Questions of the Overall Project**

The following research questions have been formulated for the overall project:

- i. What is the current reality for severely injured patients regarding their return to the workforce?

- ii. Who will be able to return to work, and when?
- iii. What influencing factors (e.g., patient, occupation, accident circumstances, injury patterns, and therapy across different sectors) exist concerning the restoration of work ability, and can these be influenced?
- iv. How does health-related quality of life (hrQoL) develop over time following a severe injury until work ability is restored?
- v. What characterizes favorable and unfavorable patient pathways and trajectories?

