## **6.3 Sample Size Calculation**

### **6.3.1 Sample Size Calculation for Prospective Cohort Study**

As severe injuries can occur in different body regions, the present cohort is considered heterogeneous. Therefore, the cohort must be large enough to allow for analyses of patient- and injury-specific subgroups (for example, traumatic brain injury), as well as the examination of socioeconomic and psychosocial factors. With a total of  $n=1000$  evaluable cases (with complete follow-up), prevalences of 10% can be reported with an accuracy of  $\pm 2\%$  (95% confidence interval), prevalences of 20% with  $\pm 2.5\%$ , and prevalences of 50% with  $\pm 3\%$ . In subgroups of 300 cases, there is still an accuracy of  $\pm 3.5/4.5/5.5\%$  for the aforementioned prevalences.

For the multivariate analyses of risk factors, a number of 5-10 patients per factor with an “event” (in this case, work ability) should be available. If approximately 30% of patients have not resumed work, about 30 predictors could be investigated across the entire cohort, which seems sufficient.

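### The time-to-work-ability analysis drops non-returners instead of censoring them, so its Kaplan-Meier curve always reaches 100% and its hazard ratios are biased, typically towards 1 under proportional hazards

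*Protocol*

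**What the plan says.** Protocol section 7.2 plans three analyses of work ability in the prospective cohort.

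- A description over the three follow-up points, stated to cover all patients.
- A logistic regression with "AF up to 18 months after trauma as a yes/no criterion" as the outcome.
- A time analysis: "Only patients with regaining AF: Time until AF as a dependent variable, Kaplan-Meier curves for description, Cox regression for multivariate analysis, predictors as above".

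The first bullet names all patients and the third names returners only, so the restriction is a stated choice of analysis set and not a detail left open. Nothing else in the protocol brings non-returners into the time analysis as censored observations.

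On timing, "Follow-up assessments will be conducted 6, 12, and 18 months after the trauma". Section 5.1 asks: "Who will be able to return to work, and when". On the expected return share, section 6.3.1 plans on 1000 "evaluable cases (with complete follow-up") and says: "If approximately 30% of patients have not resumed work, about 30 predictors could be investigated across the entire cohort". That implies about 70% back at work. Section 4 also cites a pilot study in which "only about 30% of all severely injured patients in Germany are able to work again two years after an accident".

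**The concern.** The analysis set is chosen on the outcome, and survival methods are then applied to it. This has two consequences.

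- **Kaplan-Meier.** Every retained patient has the event and nobody is censored. The estimate is simply the empirical distribution of return times among those who returned. It ends at 100% and says nothing about how many patients are back by a given month.
- **Cox regression.** Patients who stay in the risk set without returning are the evidence of a low hazard. Once they are removed, a factor that slows return mostly shifts patients out of the analysis set, and little of its effect is left in the hazard ratio.

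Membership of the returner group is also fixed by the 18-month window. A patient who returns in month 20 is excluded for being slow, so the return times are right-truncated, and an ordinary Cox model makes no allowance for that.

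At stake are the reported time course of return and the list of factors said to speed or delay it.

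**Working it through.** **Inputs from the protocol.** Window of 18 months (7.2); 1000 evaluable patients (6.3.1); about 30% not resumed, so about 70% return (6.3.1). Other return shares in section 4: about 30% at two years (pilot study); 58.5% full-time at 15 months, or 58.5 + 21.5 = 80% with part-time work added (Dutch study).

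**Assumed, because the protocol gives no values.** Exponential time to AF, a binary factor with 50% prevalence, HRs as shown, and an exactly known date of return.

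**The protocol's own figure.** 1000 × 0.30 / 10 = 30 predictors, which reproduces the stated number and confirms the 30% non-return planning value. No figure is stated for the time analysis itself.

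**Step 1: end of the curve.** With no censoring, the estimated cumulative return at the last observed return is 100% for any true return share. This is exact and needs no distributional assumption. With all patients kept, the estimate at 18 months is the true share, 70% at the planning value.

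**Step 2: medians.** For an exponential time with return share p by 18 months, λ = −ln(1 − p)/18. The true median is ln 2/λ. The median among returners solves F(t) = p/2, so t = −ln(1 − p/2)/λ.

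- p = 0.70: λ = 1.2040/18 = 0.0669. True median 0.6931/0.0669 = 10.4 months; among returners 0.4308/0.0669 = 6.4 months.
- p = 0.30 (sensitivity): λ = 0.3567/18 = 0.0198. True median about 35 months, so not reached within follow-up; among returners 8.2 months.

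**Step 3: hazard ratios.** Simulation under proportional hazards with n = 1000, baseline hazard set to give the stated overall return share, and Cox models fitted to all patients (non-returners censored at 18 months) and to returners only:

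| Return by 18 months | True HR | All patients | Returners only |
|---|---|---|---|
| 70% (planning value) | 0.50 | 0.50 | 0.80 |
| 70% | 2.00 | 2.00 | 1.25 |
| 80% | 0.50 | 0.50 | 0.74 |
| 58.5% | 0.50 | 0.50 | 0.85 |
| 30% (sensitivity) | 0.50 | 0.50 | about 0.94 |

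**Step 4: power.** For HR 0.70 and n = 1000 at 70% return, power is about 100% with all patients and about 30% with returners only (26% to 33% across simulation runs). Both analyses contain the same events, about 0.70 × 1000 = 700, so the restriction removes risk-set information and gains nothing.

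**Step 5: the logistic regression in the same scenario.** At 70% return and HR 0.70, the two groups return at about 76.4% and 63.6%. The odds ratio is (0.636/0.364)/(0.764/0.236) ≈ 0.54, with about 99% power. At 30% return, power is about 86%.

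**Step 6: does the bias always go towards 1?** No. Three cases were tried in which a fixed share of patients never returns:

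| What the factor affects | HR, all patients | HR, returners only |
|---|---|---|
| Only whether patients return (80% v 60%) | 0.61 | 1.00 |
| Only timing among returners | 0.91 | 0.77 |
| Whether and when, in opposite directions | 0.69 | 1.46 |

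**The case against.** The best defence is that section 7.2 is a two-part plan: logistic regression for whether patients return, then a time model for when, among those who do. Much of this stands. A reader might infer from the restriction that a barrier preventing return altogether would go unseen, or that all of the work-ability questions are answered with bias. The protocol does not support either reading. The logistic regression needs non-returners by its nature and uses the same predictors, and Step 5 shows that it keeps high power in the very scenario where the restricted Cox model loses it. The all-patients description also reports work ability at each visit.

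Three further points are fair. First, the pull towards 1 holds under proportional hazards and is not a law for every data structure. Second, the 30% pilot figure refers to two years and to all severely injured patients, whereas the cohort is aged 18 to 55 with an 18-month window, so it serves only as a sensitivity value. Third, the insurance-data arm separately examines recovery of work capacity over three years.

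The two-part reading does not rescue the time model. The returner group is defined by the 18-month cut-off, so the times are truncated, and nothing in section 7.2 labels the curve or the hazard ratios as conditional on return within that window. As written, they would be read as time to AF and predictors of time to AF.

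**Conclusion.** The rule is wrong as written, but its reach is limited to the time-to-AF analysis in the prospective cohort: the question of when in research question ii, and the predictors of time to AF. Who returns, and which factors bear on returning, remain addressed by the logistic regression.

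The Kaplan-Meier defect is exact. The sizes of the median shift, the hazard-ratio bias and the power loss rest on the assumptions listed in the working. Of these, only the 70% return share comes from the cohort's own planning. With more non-return the bias grows, and with less it shrinks (HR 0.50 appears as 0.74 at 80% return). Outside proportional hazards its direction cannot be guaranteed, which makes the restricted hazard ratios harder to interpret, not safer.

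**What to change.** In section 7.2, delete the restriction to patients who regained AF. Run Kaplan-Meier (shown as 1 minus survival) and Cox regression on all cohort patients, with regained AF as the event. Censor non-returners at 18 months and patients lost earlier at their last completed follow-up.

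A description of time among returners may stay if it is labelled as conditional on return by 18 months and its results are not presented as predictors of time to AF.

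The cost is a change of wording. No new data are needed, since the planned analysis already presupposes a time of return for each returner and the follow-up visits supply the censoring times. The reported return curves will look less favourable, because they will level off at the actual return share.

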## **Interim Evaluation**

An interim evaluation of the study results will take place (after the 6-month and 12-month follow-ups), where the results (content-wise) from the follow-ups will be analyzed and compared with the findings from the patient and expert interviews (see Ethics Application 1 – Qualitative Study Component). These results will be supplemented with insights from the routine data analysis (October 2022 to June 2023) and interdisciplinary evaluations of the same, involving intersectoral experts. This may lead to an expansion of the PREMs and PROMs used in the questionnaire (Development of Questionnaire Version 1.1), which will then be employed in the 18-month follow-up. The goal of the interim evaluation is to determine whether further aspects relevant to the recovery process, health-related quality of life, and the regaining of work capacity have emerged in discussions with patients that were not included in the previous questionnaire and can be added as "free text." This may result in the need to adjust the PROMs and PREMs. A revised version of the PROMs and PREMs is expected to be used in the 18-month follow-up.

Figure 3: Flow of the Prospective Cohort Study

After the follow-up period, the contributors from the study clinics will share their experiences regarding the data collection, patient feedback, and their personal assessment of the data collection processes through an online survey.

The evaluation of the prospective study will commence with the preparation of the analysis algorithms in the 4th project quarter (2023). Interim results will contribute to the temporal and content characterization of patient pathways and the care reality of severely and critically injured GKV patients.

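### Hypothesis 2 and the project goal need determinants of hrQoL, but section 7.2 models only work ability; separately, nothing keeps the scored items fixed for the 18-month visit

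*Protocol*

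**What the plan says.** Protocol section 2.1 names hrQoL and restored work ability as the two patient-relevant endpoints, and section 5 sets determinants of both as the short-term goal. Tab. 2 (section 5.2) states as Hypothesis 2: "These factors also play a relevant role in the post-traumatic condition of the patient regarding hrQoL". Here the factors are the modifiable ones in the cross-sector treatment process from Hypothesis 1. Hypothesis 3 reads: "PREMs assist in identifying such factors and in developing recommendations and measures to improve patient care". Research question iv (section 5.1) asks: "How does health-related quality of life (hrQoL) develop over time following a severe injury until work ability is restored".

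Section 7.2 contains four analysis items:

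- Course: "description of the regaining of work ability (AF) and health-related quality of life over time (3 follow-up points; descriptive statistics").
- Predictors of AF: "AF up to 18 months after trauma as a yes/no criterion; univariate and multivariate analysis (logistic regression) of possible predictors", with "classification of predictors into the categories: patient, profession, pre-hospital, clinic, post-acute therapy, presence of psychological problems (from QoL assessment at follow-up time").
- Time until AF: Kaplan-Meier curves and Cox regression with the same predictors.
- hrQoL and PREMs: "Description at the 3 follow-up points, correlation with AF as subgroup comparisons at each measurement time".

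On the questionnaire, the Interim Evaluation part of section 7.1.2 places the review after the 6- and 12-month follow-ups. It says that the PROMs and PREMs may be expanded, that new aspects can be added as free text, and that an adjustment may be needed. It ends: "A revised version of the PROMs and PREMs is expected to be used in the 18-month follow-up". Section 7.1.5 names the POLO Chart as the quality-of-life instrument.

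**The concern.** Both regressions in section 7.2 have AF as the outcome. No listed analysis has hrQoL as the dependent variable, so none relates a risk factor to hrQoL. Following the section as written, the study could report that patients back at work have better or worse hrQoL than those who are not. It could not report whether the factors found for AF also matter for hrQoL, which is what Hypothesis 2 asserts and what recommendations on modifiable factors would rest on.

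The second issue is comparability. There are three follow-up measurements, and the questionnaire may change before the last one. If scored items were reworded, the change from 12 to 18 months would carry both recovery and the effect of the new wording. That could not be separated after data collection.

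**Working it through.** **1. Hypothesis against analysis.**

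| Question | Outcome needed | What section 7.2 offers |
|---|---|---|
| Hypothesis 1: factors for AF | AF | Logistic and Cox models |
| Hypothesis 2: the same factors for hrQoL | hrQoL | Nothing with hrQoL as outcome |
| Hypothesis 3: PREMs help to identify factors | AF and hrQoL, with PREMs as explanatory information | Same-visit comparison by AF status |
| Question iv: course of hrQoL | hrQoL over time | Description at three visits |

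A comparison of hrQoL between AF groups concerns two outcomes measured in the same patients. They can be associated whether or not a given treatment-pathway factor is related to hrQoL. The one place where quality-of-life information enters a model is as a predictor of AF (psychological problems), which is the opposite direction to Hypothesis 2.

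No other quantitative part fills the gap. The WIdO analysis (section 7.1.3) has work capacity and unfavourable courses as outcomes, and section 2.1 says that the data sources are not linked.

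**2. Is the sample size the obstacle?** Section 6.3.1 gives no figure for hrQoL. Its figure for the AF model reproduces: 0.30 × 1000 = 300 patients not back at work, and 300 / 10 = 30 predictors.

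As an illustration for hrQoL, assume two-sided alpha 0.05, 80% power, 1000 evaluable cases and a linear regression with 30 predictors at one visit:

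- (1.960 + 0.842)² ≈ 7.85
- Detectable partial R² for one predictor = 7.85 / (7.85 + 1000 − 30 − 1) ≈ 0.008

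For comparison, the planned AF contrast at one visit (700 against 300) detects a standardized difference of 2.80 × √(1/300 + 1/700) ≈ 0.19. The sample therefore supports an hrQoL model. What is missing is the named analysis.

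**3. Sensitivity of the 12-to-18-month change.** With n = 1000 and equal SDs, the 95% half-width of a mean change, in SD units, is 1.96 × √(2(1 − ρ)) / √1000. The correlation ρ is not in the protocol. Over an assumed range:

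- ρ = 0.3: 0.073
- ρ = 0.5: 0.062
- ρ = 0.7: 0.048

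A shift caused by rewording that exceeded about 0.05 to 0.07 SD would be larger than the sampling error and could be read as a real change.

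**4. Mixed versions within the 18-month visit.** Let accrual be uniform over A months, and let version 1.1 be released once the last patient has had the 12-month visit, at month A + 12. A patient injured at month e has the 18-month visit at e + 18. That is before release if e < A − 6, so the share on the old version is (A − 6) / A:

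- A = 12 (the one-year phase in section 6.3.1): 6/12 = 50%
- A = 9: 3/9 = 33%
- A = 6: 0%

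Preparation time after the last visit raises these shares and earlier release lowers them. But if version 1.1 had to be ready at month 18 so that everyone receives it, then with A = 12 only patients injured in months 0 to 6 (50%) would have reached 12 months.

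**The case against.** A reader might infer that Hypothesis 2, Hypothesis 3 and question iv all go unanswered, and that the hrQoL course will rest on non-equivalent measurements. The protocol does not support that.

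- Question iv is descriptive, and the first item of section 7.2 describes hrQoL over time. It gets a group-level answer. A within-patient analysis and a link to the time when work ability returns are not stated, and the choice of model for that could be left to an SAP.
- Hypothesis 3 belongs to a mixed-method project and says only that PREMs assist. PREMs are compared by AF status and feed the interim evaluation. The predictor categories are defined by content, so PREM items on the acute clinic or the patient pathway could fall under them. The text neither includes nor excludes them.
- The interim evaluation speaks mainly of expansion and free text, and added items do not disturb existing scores. Nothing says that the POLO Chart will be reworded or rescored.
- The 50% depends on uniform accrual over a full year and on release after the last 12-month visit. Neither is stated, and section 6.3.1 thinks recruitment could be shorter.

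All four objections stand. They do not touch two points. Section 7.2 is not silent on hrQoL: it states an analysis, and that analysis does not match Hypothesis 2. An SAP, which is not at hand, could add the model, but the protocol's own statement would still need correcting. And the protocol foresees adjustment and expects a revised version without protecting the scored items.

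**Conclusion.** The point holds in two parts. First, one of the three working hypotheses (Hypothesis 2), together with the hrQoL half of the project goal, has no matching analysis in section 7.2. This follows from the text and needs no assumption. For Hypothesis 3 the weakness is smaller: no adjusted, time-ordered contribution of PREMs is assured.

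Second, comparability of the 18-month scores is unprotected. The harm is conditional: it arises only if scored items are changed. In that case between 0% and 50% of patients could be on the old version at 18 months, for 6 to 12 months of uniform accrual with release after the last 12-month visit. These shares are illustrations, not protocol figures. No arithmetic error is involved. The changes should be made, and the second must be settled before version 1.1 is used.

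**What to change.** **Section 7.2.** Add a longitudinal model, for example a linear mixed model, of the POLO Chart hrQoL score at 6, 12 and 18 months on time and the same predictor categories as the AF model. Include post-acute therapy factors recorded before the hrQoL measurement concerned; restricting the model to what is known at discharge would drop many of the factors that Hypothesis 2 is about. Leave out psychological problems taken from the same quality-of-life assessment, because they are part of the outcome. PREM scores from an earlier visit may be entered as predictors of later AF and later hrQoL, so that Hypothesis 3 gets an adjusted, time-ordered analysis besides the same-visit comparisons.

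**Interim Evaluation (section 7.1.2).** State that all scored version 1.0 items stay unchanged at 18 months, that version 1.1 only appends items, that the version is recorded per patient, and that appended items are analysed descriptively only.

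**Cost.** Modest extra analysis on data already planned, with no added patients or visits. The 18-month questionnaire may become slightly longer, to be kept within the 30 minutes in section 7.1.5, and the interim evaluation gives up the option of rewording existing items.
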